### 12.24 Case Management Utilization

Difference in mean cumulative hours spent on case management during the TDTP by the Training Program Coordinator, where ***hours spent by the Training Program Coordinator on case management will be recorded prospectively by the Training Program Coordinator using the self-report tool.*** Case management-related activities represent all out-of-class activities that the Training Program Coordinator undertakes to individually support the apprentices during the TDTP. The Training Program Coordinator will record time commitments in 0.25 hours increments, rounded up to the nearest quarter hour. For example, if the Training Program Coordinator spends 20 minutes supporting an apprentice, they would record 0.5 hours case management-related activity.

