## 7.2 Secondary

1) To compare the effect ICM^10^ and ICM^01^ versus BCM on time to access mental health & addiction services

2) To compare the effect ICM^10^ and ICM^01^ versus BCM on utilization of healthcare visits

3) To compare the effect ICM^10^ and ICM^01^ versus BCM on National Centre for Vocational Education Research Student Outcomes Survey Satisfaction scores

4) To compare the effect ICM^10^ and ICM^01^ versus BCM on mean hours spent on case management by the Case Manager

5) To compare the effect of ICM^11^ versus ICM^10^ and ICM^01^ on time to access mental health & addiction services

6) To compare the effect of ICM^11^ versus ICM^10^ and ICM^01^ on utilization of healthcare visits

7) To compare the effect of ICM^11^ versus ICM^10^ and ICM^01^ on National Centre for Vocational Education Research Student Outcomes Survey Satisfaction scores

8) To compare the effect of ICM^11^ versus ICM^10^ and ICM^01^ on mean hours spent on case management by the Case Manager

9) To measure acceptability of using self-report tool for distress by apprentices and Case Manager

10) To measure feasibility of using self-report tool for distress by apprentices and Case Manager

11) To measure compliance of using self-report tool for distress by apprentices

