
## 11.12 Web-based, self-report tool for distress

The Distress Thermometer screening tool will be integrated into a web-based, self-reporting tool that apprentices will be asked to complete on a daily basis (Monday to Thursday) prior to attending their in-class or on-site session for the 12-week duration of the TDTP. Apprentices whose cohorts are randomized to either ICM^10^ or ICM^11^ will be provided with a tablet computer to access the Distress Thermometer screening tool. Apprentices will login using a unique username and password system. The Case Manager will have immediate access to each apprentice’s daily distress score, including all of their previous scores. The scores will be prioritized according to the following criteria:

1. High Priority Distress score ≥ 4 + Answer “Yes” to last question, or

Answer “Yes” to last question

A referral may also be made if the apprentice’s distress level is escalating defined as a change of ≥ 2 on the distress score from previous day.

2. Medium Priority Distress score≥4 + Answer “No” to last question

3. Low Priority Distress score ≤3 + Answer “No” to last question

The Case Manager will immediately contact (by phone) all apprentices in the high priority group to coordinate a care management plan personalized for their identified stressor(s). For those apprentices identified as medium priority, a one-on-one in-person meeting with the Case Manager will be scheduled to occur within 48 business hours in order to coordinate a personalized care management plan for their identified stressor(s). For those apprentices identified as low priority, a quick check-in with the Case Manager will take place within the work week to determine if any special care management issues need to be addressed. The care management plan is not dictated by the study but is left to the discretion of the Case Manager and apprentice. The care management plan will be documented within the web-based, self-report tool.

For those apprentices who do not compete a daily assessment by 8 am, the Case Manager will reach out by email/phone immediately to the apprentice to enquire about their status. For those apprentices experiencing severe distress, they have the option of directly contacting (email/phone) the Case Manager instead of completing the Distress Thermometer screening tool.

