| Date/Time (Action) | ddmmyy:hh | Continuous |
| Case management time | 0.15 hr units | Continuous |
| Apprentice attendance (Daily (M-F) for 12-week TDTP) | Yes | Categorical |
|  | No |  |
|  |  |  |

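### Case-management time is always rounded up to a quarter hour in Section 12.24 but held in 0.15 h units in Section 18.11: hours are overstated, and the arm difference may be distorted

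*Protocol*

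**What the plan says.** Section 12.24 defines the outcome as "Difference in mean cumulative hours spent on case management during the TDTP by the Training Program Coordinator". The recording rule is "The Training Program Coordinator will record time commitments in 0.25 hours increments, rounded up to the nearest quarter hour", and the example reads: "if the Training Program Coordinator spends 20 minutes supporting an apprentice, they would record 0.5 hours case management-related activity". Only activity outside class counts.

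The data table in Section 18.11 lists the variable as "Case management time | 0.15 hr units | Continuous", within the block of fields headed Case Manager. Section 20.12d analyses the recorded cumulative hours by linear regression.

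Section 11.12 describes the contacts that the tool triggers. Apprentices are asked to fill in the screen "complete on a daily basis (Monday to Thursday) prior to attending their in-class or on-site session for the 12-week duration of the TDTP". For a low-priority result, "a quick check-in with the Case Manager will take place within the work week". For a screen not done by 8 am, "the Case Manager will reach out by email/phone immediately to the apprentice to enquire about their status". Higher priorities lead to a phone call or a one-to-one meeting. Section 5.3 describes the brokered (BCM) comparator as bi-weekly meetings, Slack check-ins whose frequency is left unfilled, frequent site visits and monitoring of weekly mentor feedback.

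The protocol names two roles for this outcome. Objective 4 in Section 7.2 is "To compare the effect ICM^10^ and ICM^01^ versus BCM on mean hours spent on case management by the Case Manager", and objective 8 uses the same role. Sections 12.24 and 20.12d count the Training Program Coordinator's hours.

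**The concern.** The endpoint is a sum of entries, each subject to an error that is never negative. Such an error does not cancel within an apprentice and does not shrink with more apprentices. If each contact is one entry, the excess grows with the number of contacts and not with the time spent. An intervention that creates many brief contacts could then look more labour-intensive than it is.

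The second problem is a plain contradiction: the outcome definition and the data specification give different units for one variable. Recording is prospective, so minutes rounded away at entry cannot be recovered in the analysis. This is the only listed outcome that measures staff time.

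**Working it through.** **1. Reproduce the protocol's example.** Recorded hours = u × ceil(minutes / (60u)), where u is the unit in hours. With u = 0.25 and 20 minutes: ceil(20/15) = 2, and 2 × 0.25 = 0.50 h, as Section 12.24 states. True time is 20/60 = 0.333 h, so the excess is 0.167 h, or 50%. Rounding to the nearest quarter would give 0.25 h. The rule is therefore a one-sided ceiling.

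**2. Compare the two units.** 0.25/0.15 = 1.67 and 0.50/0.15 = 3.33. Neither is a whole number, so neither the smallest value allowed by Section 12.24 nor its example value lies on the 0.15 h (9-minute) grid. If rounding up also applied to 0.15 h units, which Section 18.11 does not say, 20 minutes would be 0.45 h instead of 0.50 h, and 5 minutes would be 0.15 h instead of 0.25 h.

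**3. Excess per entry under Section 12.24.**

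| True minutes | True h | Recorded h | Excess h | Recorded/true |
| --- | --- | --- | --- | --- |
| 2 | 0.033 | 0.25 | 0.217 | 7.5 |
| 5 | 0.083 | 0.25 | 0.167 | 3.0 |
| 10 | 0.167 | 0.25 | 0.083 | 1.5 |
| 15 | 0.250 | 0.25 | 0 | 1.0 |
| 16 | 0.267 | 0.50 | 0.233 | 1.9 |
| 20 | 0.333 | 0.50 | 0.167 | 1.5 |
| 30 | 0.500 | 0.50 | 0 | 1.0 |

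The excess is never negative and always below 0.25 h. The relative error is largest for the shortest contacts.

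**4. Effect on the arm difference.** Bias = total excess in the tool arm minus total excess in the comparator. The protocol gives no counts or durations, so the following are assumptions: every short contact lasts 5 minutes and is its own entry. Then bias = (tool contacts − comparator contacts) × 0.167 h per apprentice.

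| Tool contacts | Comparator contacts | True difference (h) | Recorded difference (h) | Bias (h) |
| --- | --- | --- | --- | --- |
| 24 | 12 | +1.0 | +3.0 | +2.0 |
| 24 | 24 | 0 | 0 | 0 |
| 12 | 24 | −1.0 | −3.0 | −2.0 |

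Equal counts do not guarantee zero bias. Twelve 5-minute entries carry 12 × 0.167 = 2.0 h of excess, and twelve 15-minute entries carry none.

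**5. Level of rounding.** Section 12.24 applies the rule to time commitments. Its example fits a single episode of support, but the section does not say whether an entry is a contact, a day or a week. Three 5-minute contacts on one day give 3 × 0.25 = 0.75 h if rounded singly, and 0.25 h (no excess) if the day's 15 minutes are rounded once.

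**The case against.** The strongest reply is that the same rule applies in all four cells, so it need not bias the comparison at all. That is correct. The comparator also has short contacts, and if the tool replaces Slack check-ins the bias shrinks or reverses.

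A reader might infer a definite penalty against the tool of 2 to 3 h per apprentice. One set of assumptions gives that. In the tool arm, 12 weekly 5-minute check-ins and 5 missed-screen calls of 2 minutes are recorded as 17 × 0.25 = 4.25 h against a true 1.17 h, an excess of 3.08 h. In BCM, six meetings of 20 to 30 minutes are recorded as 3.0 h against a true 2.0 to 3.0 h, an excess of 0 to 1.0 h. The documents do not support these inputs:

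- They give BCM no short contacts. Twelve weekly 5-minute Slack check-ins would add 12 × 0.167 = 2.0 h of excess to BCM and leave a bias of about 0.1 to 1.1 h.
- They read bi-weekly as every two weeks. If it means twice a week, 24 meetings of 20 minutes carry 24 × 0.167 = 4.0 h of excess, and the sign reverses.
- They give the tool arm no usual meetings, although Section 1.1 describes the tool as added to usual case management.
- They count every check-in, although Section 12.24 excludes in-class activity.

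A reader might also infer that this outcome decides adoption of the tool. Section 30 ties adoption to superior effectiveness and does not mention staff hours.

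On the unit, the field is typed as continuous and nothing says that the form would reject 0.25, so it would be too strong to say that the value cannot be entered. The specifications still disagree. On the roles, the two titles look interchangeable: objectives 9 and 10 say Case Manager where Sections 12.25 and 12.26 say Training Program Coordinator. This may be inconsistent naming only and does not show that hours would be omitted.

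**Conclusion.** Two defects follow from the text alone. The unit in Section 12.24 contradicts the unit in Section 18.11. The ceiling rule overstates recorded hours in every arm, by less than 0.25 h per entry, with a 50% overstatement in the protocol's own example.

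A distorted arm difference is possible but not demonstrated. It requires that the number or length of entries differ between arms, and its scaling with contacts rests on reading the rule as applying to each contact. An overstatement of the tool's workload is the likelier direction, because the tool adds brief contacts to usual care. Any figure in hours is an illustration under assumed counts and durations.

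The outcome is secondary and no primary conclusion depends on it. The change is still worth making before data capture, because it is nearly free and rounded data cannot be repaired later.

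**What to change.** In Sections 12.24 and 18.11, use one unit: record the actual minutes of each case-management activity without rounding, sum them per apprentice over the 12-week program, and convert the total to hours once. Delete the quarter-hour round-up rule with its example, and the 0.15 h unit.

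In Sections 7.2, 12.24 and 20.12d, use one role title, or state that the time of whoever delivers case management to the apprentice counts in all four cells.

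The cost is one field format and a few sentences. The downside is that staff enter minutes instead of picking an increment.

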### 12.25 Acceptability of self-report tool

To measure the acceptability of using the Distress Thermometer screening tool by apprentices and the Training Program Coordinator, where ***acceptability is measured using a 2-item questionnaire.*** The 2-item questionnaire was developed to measure acceptability of the Distress Thermometer tool among different user groups (22). The 2-items are:

1. Rate the degree of difficulty you encountered in using (monitoring) the Distress Thermometer screening tool.

The response options are: *Very easy (score=1); Somewhat easy; Somewhat hard; Very hard (score=4)*

2. To what extent did completing (monitoring) the Distress Thermometer screening tool bother you?

The response options are: *Didn’t bother me at all (score=1); Bothered me a little bit; Bothered me a lot (score=3)*

### 12.26 Feasibility of self-report tool

To measure the feasibility of using the Distress Thermometer screening tool by apprentices and the Training Program Coordinator, where ***feasibility is measured using a 1-item questionnaire.*** The 1-item questionnaire was developed to measure feasibility of the Distress Thermometer tool among different user groups (22). The 1-item questionnaire is:

1. How feasible was it to use (monitor) the Distress Thermometer on a daily basis?

The response options are: *Very feasible (score=1); Somewhat feasible; Somewhat infeasible; Very infeasible (score=4)*

### 12.27 Compliance of self-report tool

To measure apprentices’ compliance with the Distress Thermometer screening tool, where ***compliance is defined as the ratio of completed daily screens relative to the total number of TDTP days.*** The criteria for a completed daily screen include filling out the distress score, the source of distress, and the ‘yes/no’ question, or identifying the reason for not completing those items.

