## 11.3 Compliance

To promote study enrollment and adherence with study-related tasks, each enrolled apprentice will be provided with a tablet computer for the duration of the TDTP to support their participation and promote adherence to daily screening with the Distress Thermometer self-reporting tool. Apprentices who complete ≥ 90% of their daily Distress Thermometer screens will receive $50 for their time and effort and be enrolled in a draw for 5 tablet computers. The Apprentices enrolled in ICM^10^ and ICM^11^ do have the option of not completing the Distress Thermometer screening tool. These apprentices will be asked to relate the reason for each episode of non-compliance from a fixed list available in the self-report tool. Apprentices who choose not to complete the Distress Thermometer screening tool but document the reason will be considered to be compliant for that episode.

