# 12 Outcomes

## 12.1 Primary outcome measures

### 12.11 Program attendance

Difference in proportion of absence-free program days (AFDs) at 12 weeks from the start date of the TDTP, where ***absence-free days are defined by the cumulative number of days of program attendance during the 12-week study period.*** The potential number of AFDs for each apprentice is the cumulative number of program days that the apprentice is alive during the 12-week TDTP, with a maximum of 48 days (=12 weeks x 4 days/week). A day is defined as an 8–10-hour work-day during the TDTP from Monday to Thursday. An apprentice is considered to have attended a work-day as long as the Case Manager or their construction supervisor documents their attendance.

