## 14.2 Difference in proportions of TDTP completion

Historical cohorts have demonstrated variation in program completion proportions but have been generally observed at a 75-80% graduation / completion rate. In this cluster randomized trial comparing the difference in proportions of TDTP completion, we define an *a priori* difference of ≥ 0.1 in completion proportions as the lower limit of a minimally significant difference (24). This is opinion-based on an informal survey of TDTP stakeholders. Given the same fixed sample and cohort size estimates discussed in Section 14.1, we performed a sensitivity analysis to determine the power to observe a difference in program completion proportions ≥ 0.1 using different control group completion rates with an $\alpha$-level 0.05**.**  As can be seen in the following table, a difference in completion proportions of 0.1 would be detected with power ≥ 80% as long as the control group completion proportion was ≥ 0.8, a reasonable assumption given the historically observed program completion proportions.

|  | **Scenarios**^1^ | | | | | | |
| --- | --- | --- | --- | --- | --- | --- | --- |
| **Variables** | 1 | 2 | 3 | 4 | 5 | 6 | 7 |
| Test Significance Level, α​ | 0.05 | 0.05 | 0.05 | 0.05 | 0.05 | 0.05 | 0.05 |
| 1 or 2-Sided Test?​ | Two | Two | Two | Two | Two | Two | Two |
| Control Group Proportion (p2)​ | 0.75 | 0.75 | 0.75 | 0.75 | 0.8 | 0.8 | 0.8 |
| Test Statistic under H0​ | 0 | 0 | 0 | 0 | 0 | 0 | 0 |
| Test Statistic under H1​ | 0.1 | 0.1 | 0.1 | 0.1 | 0.1 | 0.1 | 0.1 |
| Intracluster Correlation (ICC)​ | 0 | 0.05 | 0 | 0 | 0 | 0 | 0 |
| Clusters in Treatment Group (K1)​ | 20 | 20 | 33 | 25 | 20 | 33 | 25 |
| Clusters in Control Group (K2)​ | 20 | 20 | 33 | 25 | 20 | 33 | 25 |
| Cluster Ratio (K2/K1)​ | 1 | 1 | 1 | 1 | 1 | 1 | 1 |
| Cluster Sample Size in Treatment Group (M1)​ | 10 | 10 | 6 | 8 | 10 | 6 | 8 |
| Cluster Sample Size in Control Group (M2)​ | 10 | 10 | 6 | 8 | 10 | 6 | 8 |
| Cluster Sample Size Ratio (M2/M1)​ | 1 | 1 | 1 | 1 | 1 | 1 | 1 |
| Power (%)​ | 70.6 | 54.6 | 70.2 | 70.6 | 80.2 | 79.8 | 80.2 |

^1^ Highlighted cells (Yellow) represent changes from previous scenario

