# 15 Recruitment

To be eligible for TDTP enrollment, individuals must be Canadian, female, black, from a racialized community, an immigrant, and/or Indigenous. Eligible individuals must submit to an interview with Community Builders®. Successful candidates must demonstrate that they are a good fit for the TDTP by showing, at a minimum, an interest in the construction trades and possessing some basic English or French-speaking and writing skills. Enrollment in the TDTP is not contingent on eligible individuals agreeing to participate in the TeachMeToBuild study. Individuals enrolled in the TDTP whose cohort is randomized to the Distress Thermometer screening tool intervention will be introduced to the TeachMeToBuild study during their initial TDTP orientation. The case managers will use the expressed consent powerpoint presentation to introduce the study to the students. During this introduction, all TDTP students will be informed that their participation in the study is voluntary and refusal to enrol or withdraw after study enrollment will not affect their subsequent TDTP participation or outcomes. After this introduction, each individual will be provided with the contact information (email and telephone number) for a study team member that can be reached to further discuss the study and possible enrollment. For those individuals who contact the study team member, an in-person meeting or audio/video teleconference will be scheduled. During this meeting, the study team member will discuss the study rationale, objectives, participant responsibilities, data collection, risks and benefits. During this meeting, the study team member will encourage and answer study-related questions. For interested individuals, the study team member will review the informed consent form (ICF) and answer all questions. Interested individuals will be provided with a paper/electronic copy of the ICF to review, and a subsequent follow-up in-person or audio/video teleconference meeting in 72 hours (business days) will be scheduled between the study team member and the interested individual to determine their interest to enroll in the TeachMeToBuild study. All TDTP students will be reminded by the study team member during the meetings that study participation is voluntary and refusal to enrol or withdraw after study enrollment will not adversely affect their subsequent TDTP participation or outcomes. To withdraw from the study, the participant will inform the case manager who will then inform the study team members.

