#### 20.12f Compliance of self-report tool

We will use linear multivariate regression analysis to model the difference in mean compliance rates for the Distress Thermometer self-report tool. The interventions (Distress thermometer and MH&A) will be included as well as a variable for their interaction effect. We will also include time period (year-quarter) and an interaction term between the time period and each intervention (Distress thermometer and MH&A).

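### Section 12.27 divides tool compliance by all program days, so days after leaving the program or the study count as non-compliance and the ratio mixes tool use with retention

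*Protocol*

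**What the plan says.** Section 12.27 fixes the measure: "compliance is defined as the ratio of completed daily screens relative to the total number of TDTP days". A screen counts as completed if all three items are filled in, "or identifying the reason for not completing those items". Section 20.12f will then "model the difference in mean compliance rates for the Distress Thermometer self-report tool" by linear regression on both interventions, their interaction and time period.

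The number of program days is not given in 12.27. Section 11.12 asks apprentices to use the tool before each session, "complete on a daily basis (Monday to Thursday"), for 12 weeks. Section 12.11 counts potential attendance days per apprentice "with a maximum of 48 days (=12 weeks x 4 days/week"). Section 13, however, shows the intervention period as days 1-60 (M-F), and Section 18.11 records daily attendance M-F.

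Several sections describe apprentices who stop having screens to make:

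- Section 14.2 reports that completion was "generally observed at a 75-80% graduation / completion rate".
- Section 12.12 counts as drop-outs those who miss more than half of training days and those who choose to leave, except for a job or school.
- Section 11.2 moves some apprentices out of their cohort and into a later one.
- Section 18.22 lets apprentices withdraw from the study while staying in the program, and keeps their data up to that point in the analysis.

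On consent, Section 13 places it on day 0. Section 15 introduces the study at orientation, follows with a meeting, and then says that "a subsequent follow-up in-person or audio/video teleconference meeting in 72 hours (business days) will be scheduled".

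Section 11.3 adds a payment: "Apprentices who complete ≥ 90% of their daily Distress Thermometer screens will receive $50". It gives no denominator for that percentage.

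**The concern.** A screen is completed before a session, so an apprentice who has left has none to complete, and one who has withdrawn from the study is no longer asked. Under 12.27 those days stay in the denominator while the numerator can no longer grow. An apprentice who screened on every day available and left at week 6 would score 50%.

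The average then answers two questions at once: how well the tool was used while it was available, and how long people stayed. The second is already measured by program completion, a primary outcome. This matters most for comparisons. Only the ICM^10^ and ICM^11^ cohorts have the tool, so the informative contrast in 20.12f is between those two. Section 6.2 hypothesises less drop-out in ICM^11^. If that is true, ICM^11^ would also show better compliance even where the tool was used identically.

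**Working it through.** **The plan's own figure.** 12 weeks x 4 days = 48 program days, which agrees with Section 12.11. On the M-F schedule of Sections 13 and 18.11 it is 12 x 5 = 60. An apprentice who makes all 48 Monday-Thursday screens scores 48/48 = 100% on one reading and 48/60 = 80% on the other.

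**Inputs for the size.**

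- Share leaving, d: 0.20-0.25. This is the complement of the 75-80% completion in Section 14.2, used as a stand-in because the share who actually leave is not given.
- Fraction of the program done at leaving, f: not in the protocol. Assumed 1/4, 1/2, 3/4, or uniform over the 48 days.
- Program days lost before consent, L: 0, following Section 13.

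**Relative understatement.** Mean available days divided by 48 is (1 - d) + d·f when L = 0, so the understatement is d(1 - f).

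| Leaving point | d = 0.20 | d = 0.25 |
|---|---|---|
| f = 3/4 | 5.0% | 6.25% |
| f = 1/2 | 10.0% | 12.5% |
| f = 1/4 | 15.0% | 18.75% |

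For uniform leaving the mean leaving day is 24.5, so the available share is 1 - d(1 - 24.5/48) = 0.902 (d = 0.20) or 0.878 (d = 0.25). With an assumed true use of 90% of available days, reported compliance is 90 x 0.902 = 81.2% or 90 x 0.878 = 79.0%.

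**Contrast between the tool arms.** Take a 10-point difference in leaving, matching the minimum completion difference of 0.1 in Section 14.2, and 90% use in both arms. The artefact is 90 x 0.10 x (1 - 24.5/48) = 4.4 points for uniform leaving. It is 90 x 0.10 x 0.25 = 2.25 points if leavers go at three quarters, and 90 x 0.10 x 0.75 = 6.75 points if they go at one quarter.

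**If consent came after the start.** The understatement becomes d(1 - f) + L/48. With mid-program leaving, L = 3 gives 16-19% and L = 6 gives 22.5-25%. With L = 8 and early leaving it reaches 35%. These values of L are purely illustrative.

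**How far the ratio reflects retention.** Write the ratio as C x A, with C true use and A the available fraction, independent, with uniform leaving. Then E(A) = 1 - d/2, E(A²) = (1 - d) + d/3, and the share of variance due to leaving is mean(C)²·Var(A)/Var(CA). With mean use 0.8 and SD 0.10-0.20 the share is 51-84%. With mean 0.6-0.7 and SD 0.25-0.30 it is 21-39%.

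**Incentive.** If the denominator were 48, 90% would need 44 screens (0.9 x 48 = 43.2, rounded up). Losing 5 days before consent would cap the score at 43/48 = 89.6%, and losing 4 would leave 44/48 = 91.7%.

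**The case against.** The other side has good arguments, and several stand.

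- **An all-days ratio is legitimate as coverage.** In a pragmatic trial it shows how much of the program the tool reached, and a days-available ratio can flatter a tool that people abandon by leaving. This is a reason to report both, not to call the mixture compliance.
- **The wording might mean each apprentice's own program days.** That reading is possible and would remove the days after leaving. It would not remove the days of someone who withdraws from the study but stays in the program.
- **Non-completion is not leaving.** Those who miss more than half of the days may still be enrolled and able to screen or log a reason; for them a low ratio is real non-use. Those who leave for a job or school are not drop-outs but do lose days. The share leaving is therefore unknown, and 20-25% is a stand-in.
- **The arm contrast is already confounded with site.** ICM^10^ is in Sudbury and ICM^11^ in Barrie. This limits what any compliance comparison can show, but a retention artefact still adds to the problem.

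Three stronger readings are tempting and are not supported. First, a reader might infer that program days are certainly lost before consent. Section 13 puts consent on day 0, and Section 15 gives no date for orientation relative to the first program day, so the loss is possible but not established. For the same reason it cannot be said that late consenters are shut out of the payment, whose denominator is not stated. Second, a reader might quote a single understatement such as 10-25%. The upper part of that range needs a consent delay or early leaving that the protocol does not give. Third, a reader might say that the ratio tracks drop-out instead of tool use. For apprentices who stay throughout it does measure tool use, and the share due to leaving depends on an assumed spread.

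**Conclusion.** The point holds in limited form. As written, 12.27 counts days after leaving, transfer or study withdrawal as non-compliance, so the ratio measures tool use together with retention. The relative understatement is about 10-12.5% if 20-25% leave at mid-program or uniformly with consent on day 0, and 5-19% if leaving is concentrated at three quarters or one quarter of the way through. It shrinks in proportion if fewer actually leave. The between-arm artefact is about 4 points for a 10-point retention difference, at 90% use and uniform leaving.

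Two points rest on the text alone: the number of scheduled days is inconsistent (48 or 60), and the timing of consent differs in certainty between Sections 13 and 15. The change is worth making because it is cheap and removes an avoidable artefact.

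**What to change.** In 12.27 and 20.12f, define compliance as completed screens divided by scheduled program days from consent and tool registration to the earliest of leaving the program, study withdrawal or week 12. Report the ratio over all scheduled days separately, labelled as coverage, with the drop-out proportion beside it in each arm.

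In the same edit:

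- state whether scheduled days are Monday to Thursday (48) or Monday to Friday (60), and align Sections 11.12, 12.11, 13 and 18.11;
- reconcile Section 13 with Section 15 on when consent is obtained relative to the first program day (the proposed denominator works either way);
- state the denominator of the 90% payment threshold in 11.3.

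The cost is a few sentences. The audit trail in Section 19 should supply registration dates, and withdrawals are reported to the study team under Section 15. A leaving date is not among the data items in 18.11 or 18.13. It should be recorded, since inferring it from the last attended day would misclassify apprentices who are absent but still enrolled. The downside is that compliance then describes only days at risk, so it must be read together with retention.
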